#### Inclusion criteria

Participants will be included when (1) 18 years or older; (2) having a documented physician-based diagnosis of T2D; and (3) having a major depressive episode according to DSM-IV criteria.

#### Exclusion criteria

Participants will be excluded from participation when any of the following criteria is present: (1) a recent history of or current use of light therapy; (2) shift worker; (3) a recent change in antidepressant or blood-glucose lowering medication or therapy (e.g. psychotherapy); (4) use of oral glucocorticoids, melatonin, or cytostatics; (5) pregnancy; (6) psychosis, mania, (probable) dementia, severe drug or alcohol abuse, delirium, and severe acute suicidality; (7) a history of light-induced migraine or epilepsy or severe side effects to light therapy in the past; (8) visual acuity <60 %, diabetic retinopathy EURODIAB grades 3, 4 or 5 (severe non-proliferative or preproliferative retinopathy, photocoagulated retinopathy, proliferative retinopathy) [44, 45], senile macula degeneration; (9) other medical condition or recent medical event that potentially compromises the effects or safety of light therapy.

There are no restrictions with respect to type of antidepressant or blood-glucose lowering medication.

### Safety

Light therapy has proven to be a patient friendly and safe intervention, with little side effects that normally resolve after discontinuation of the therapy.

The ocular safety of light therapy, however, remains matter of debate. Follow-up of patients with cumulative exposure durations up to 1250 h demonstrated that light therapy is safe in patients without pre-existing ocular abnormalities [46]. Ocular effects of light therapy in patients with pre-existing ocular abnormalities, diabetes, or in patients using photosensitising medication, however, remain under speculation [47]. Therefore, stringent ocular exclusion criteria have been defined (e.g. diabetic retinopathy EURODIAB grade 3, 4 and 5) and safety precautions have been taken, such as the use of filters that eliminate an additional part of the energetic light spectrum below 450 nm (blue light), which theoretically has the most damaging potential, in addition to the of UV-A and UV-B filters with which the light therapy lamps are normally equipped with (Fig. 3).

**Fig. 3 Fig3:**
[figure not shown]
Light spectral and relative intensity measures. Light spectral and relative intensity measures at 50 cm distance of the bright white-yellowish light condition (yellow), the dim green light condition (green) and the lamp without filter (blue)

Mania (in bipolar depressive patients) and acute suicidality have been theorised as potential psychiatric side effects of light therapy [24, 48, 49] although there is little documented evidence. The investigator will contact a participant weekly during the intervention in order to be able to intervene in case of deterioration of psychiatric symptoms.

### Intervention

The intervention will consist of light therapy for 30 min every morning, for four consecutive weeks at home. The time at which light therapy is applied in the morning will be determined according to results from the Morningness-Eveningness Questionnaire [24] to allow for accurate phase timing, but in agreement with the participant, to make sure the light therapy can be incorporated in the participant’s daily rhythm. A timer will be installed to provide a 90 min time window in which the participants can follow the 30 min of light therapy. This provides the participants with a time window of an hour to start the light therapy, which will prevent participants from taking light therapy at another time of the day. Participants will sit in front of the light boxes at a distance of 50 cm and at an angle of 45 °, while they eat breakfast or do some reading (protocol as recommended by Wirz-Justice and colleagues, 2009 [50]).

Diamond-5 SAD lightbox (CE certified; SAD Lightbox Company, Berkshire, United Kingdom) light therapy lamps will be used. The lamps will be equipped with heat-resistant filters, to create an experimental and placebo light therapy condition.

The experimental condition will be bright white-yellowish light, with an intensity of 10.000 lx at a distance of 50 cm. The lamps will be equipped with high-throughput pale yellow filters (LCT Yellow, Model 212; Lee Filters, Burbank, California, United States of America), to filter the spectrum below 450 nm for ocular safety. The circadian system appears most sensitive to light with short wavelengths and light therapy with light of around 470 nm is able to induce a substantial phase advance [51]. We therefore think filtering for ocular safety will not interfere with our hypothesis. Spectral and intensity measures are depicted in Fig. 3.

The control condition will be dim green light with an intensity of 450 lx at a distance of 50 cm. As the green part of the spectrum around 545 nm is biologically relatively inactive [51], we expect there to be no substantial effects, especially at this low intensity, although expectations will be quite comparable to white light, as was previously shown for dim red light [52]. To create the dim green light condition the lamps will be equipped with low-throughput dark green filters (Aurora Borealis Green: Model 740; Lee Filters, Burbank, California, United States of America). Spectral and intensity measures are depicted in Fig. 3.

### Compliance

Participants will be instructed by research assistants on how to follow the light therapy program. The position of the light therapy lamp and the participant during light therapy will be marked, so the participant can retake the same position day after day. The investigator will contact the participants weekly during the intervention period and compliance will be monitored and reinforced when needed.

### Randomisation

Participants will be randomly assigned to the experimental or placebo condition at a 1:1 ratio. Randomisation will be performed in blocks of 6 using a computer-generated table and will be stratified for whether a participant will or will not take part in the hyperinsulinaemic-euglycaemic clamp experiment, which will only be performed in a subgroup of the participants.

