### Blinding

Both investigators and participants will be blind with respect to the treatment conditions. Participants will be informed that two different colours of light (white-yellowish and green) will be compared, but not that a placebo condition is present, nor that the green light is less bright or less effective compared to the white-yellowish lamp. This approach is effective in avoiding differences in participants’ expectations regarding the effectiveness of the conditions, as expectations may affect treatment effects [30, 53, 54]. The investigators involved in data acquisition will be blind to the conditions, as the lamps will be delivered at the participants’ homes by independent research assistants, who are instructed not to discuss the brightness of the lamp, and participants will be instructed not refer any details of their condition to the investigators. A similar blinding procedure showed to be successful in a previous study conducted by our institute [30].

To evaluate the blinding procedure, participants’ expectations of the effect of light therapy on depressive symptoms will be measured before installation of the light therapy lamps, using an adapted version of the expectations questionnaire developed by Lieverse and colleagues, 2011 [30].

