### Sample size

A previous study on the effects of light therapy on depression in elderly patients using a comparable protocol [30] showed that direct treatment effects of light therapy on depressive symptoms were moderate (effect size 0.50 Cohen’s d), and increased during follow-up (effect size 0.91 Cohen’s d), with one-sided testing. Power calculations were based on the expected moderate effect size and a conservative repeated measures correlation of 0.6, using conventional values for α (0.05) and β (0.20), and two-tailed tests with equal groups – the sample size aimed for will be 42 participants per treatment arm. Accounting for an attrition rate of 15 %, we derive at a total sample size of 98 participants.

The question whether light therapy alters insulin sensitivity in type 2 diabetes patients with depression will be tested in a subsample of 60 participants in total. A sample size of 30 participants per treatment arm is sufficient to detect a moderate effect (0.76 Cohen’s d) of light therapy on insulin sensitivity, with conventional values for α (0.05) and β (0.20), and two-tailed tests with equal groups, assuming a dropout rate of 10 %. The hyperinsulinaemic-euglycaemic clamp experiment will thus be performed in a subgroup of the participants and participation in this procedure will be optional. Participants with difficult venous access or medical conditions that impair the safety of the procedure will be excluded from participation in the hyperinsulinaemic-euglycaemic clamp experiment.

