## Trial status

The first participant was enrolled in June 2014. At the time of submission of this study protocol participants were still being recruited.

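### A single disclosed block size of 6, in a trial whose arms differ visibly by colour, makes some assignments needlessly predictable if earlier arms leak; undisclosed, randomly varied sizes would be a cheap improvement

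*Protocol article*

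**What the plan says.** The Randomisation section gives the rule in full: "Participants will be randomly assigned to the experimental or placebo condition at a 1:1 ratio", and "Randomisation will be performed in blocks of 6 using a computer-generated table". It adds that allocation "will be stratified for whether a participant will or will not take part in the hyperinsulinaemic-euglycaemic clamp experiment". There are therefore two lists, each made of blocks with three places per arm. The section mentions no second block size and does not say that the size is withheld from anyone.

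The Sample size section sets the total at 98. It says that the insulin-sensitivity question "will be tested in a subsample of 60 participants in total", and that "participation in this procedure will be optional".

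The Intervention section describes a bright white-yellowish lamp and a dim green lamp. Under Blinding, "Participants will be informed that two different colours of light (white-yellowish and green) will be compared". Investigators who collect data are kept blind in two ways: independent assistants bring the lamps to the home, and "participants will be instructed not refer any details of their condition to the investigators". The Compliance section has the investigator contact each participant weekly during treatment. Table 1 shows telephone contacts in weeks 1, 2, 3 and 6 and visits at weeks 4 and 8.

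The Trial status section says: "At the time of submission of this study protocol participants were still being recruited".

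**The concern.** A fixed block size does little harm when the arms look alike, because an observer seldom learns any earlier assignment. Here one colour word reveals an arm to an investigator who knows the design. The people told not to say that word are in regular contact with the investigator about their lamp use. With one known block size, each disclosure also carries information about the next place in the same stratum.

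Two things would be at stake if disclosures accumulated. First, entry involves some discretion: the last exclusion criterion is a judgement, and clamp participation, which decides the list, is optional and subject to medical exclusions. Selection by predicted arm would not be undone by the intention-to-treat mixed model. Second, disclosed arms could reveal the arms of other participants in the same block and so weaken the investigators' blind for people who had disclosed nothing.

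**Working it through.** The article gives no predictability figure, so there is none to reproduce. The inputs are the block size of 6 and the 1:1 ratio (Randomisation), and the total of 98 with 60 in the clamp subsample (Sample size), which leaves 98 − 60 = 38 outside it. The leak rate q, the probability that any one earlier arm in the block is known, is an assumption, shown over a range.

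**Full knowledge (q = 1).** A 3:3 block has C(6,3) = 20 equally likely orderings. A place is certain once one arm has used its three places.

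- Place 6 is always certain: probability 1.
- Place 5 is certain if the last two places hold the same arm: 2 × C(4,3) / 20 = 8/20 = 0.4.
- Place 4 is certain if the last three places hold the same arm: 2/20 = 0.1.
- Places 1 to 3 are never certain.

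The expected number is 1 + 0.4 + 0.1 = 1.5 of 6, or 25%.

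The best guess is right with probability 0.5, 0.6, 0.6, 0.7, 0.7 and 1 at places 1 to 6. The sum is 4.1, and 4.1/6 = 68.3%, against 50% by chance.

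**In the trial.** If the strata fill as planned, 60 gives 10 full blocks, and 38 gives 6 full blocks plus 2 participants in an open block, whose places are never certain. So 16 × 1.5 = 24 assignments are certain, and 24/98 = 24.5%.

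**Partial knowledge.** A place is certain only if all three members of the exhausted arm are known, which has probability q³. The certain share of a block is therefore 0.25 × q³. Correct guessing comes from enumerating the 20 orderings with every pattern of known and unknown earlier members. The observer is taken to know the position in the block.

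| q | Certain share | Certain of 98 (24 × q³) | Guessed correctly |
|---|---|---|---|
| 1 | 25.0% | 24 | 68.3% |
| 0.75 | 10.5% | 10.1 | 62.4% |
| 0.50 | 3.1% | 3.0 | 58.4% |
| 0.25 | 0.4% | 0.4 | 54.8% |
| 0.10 | 0.03% | 0.02 | 52.2% |

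**After the change.** Block sizes of 4, 6 and 8, drawn with equal probability, were simulated in sequences of 60. The observer knows the set of sizes and every earlier arm, but not which sizes were drawn. Certain assignments are 2.3% and correct guesses 67.8%. For sequences of 38 the figures are 2.3% and 67.6%.

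The varied scheme was not simulated under partial knowledge, but a bound is available: anything certain with partial knowledge is also certain with full knowledge, so the certain share lies between 0 and about 2.3%. At q = 0.50 the gain is thus between 3.1 − 2.3 = 0.8 and 3.1 percentage points. At q = 0.25 it is at most 0.4 points.

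**The case against.** The case against is substantial. A fixed block size is a common and legitimate choice, and nothing in the article contradicts it. The people certain to know the colours are each participant, for his or her own lamp, and the delivering assistants. The assistants are independent, and nothing says that they screen, enrol or assess. The Blinding section also reports that a similar procedure worked in an earlier study at the same institute. Steering entry would take several disclosures in one block and stratum, correct tracking of the position in the list, and deliberate misuse of a judgement; clamp participation is also partly the participant's own choice. Visits take place at two locations, which are not strata, so an investigator at one location might see only part of a list; the article does not say whether staff differ. The depression outcome is self-reported. A participant who names a colour unblinds the investigator for that participant whatever the block size.

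All of this stands, and it limits the point. Three stronger readings are tempting, and the document supports none of them.

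- A reader might infer that knowing some earlier arms makes a quarter of assignments certain. The quarter needs every earlier arm in that block and stratum; with half of them known it is 3%.
- A reader might infer that the block size was in print while patients were still being enrolled. The article gives recruitment status at submission, not at publication.
- A reader might infer that it is a defect not to say who holds the list, or that eligibility is final before the draw. An article commonly leaves such details to the full protocol.

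What the objection does not remove is that the block size is stated as one fixed value, in a setting where arms are easily revealed and part of the protection is an instruction.

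**Conclusion.** The point holds as an avoidable weakness and a cheap improvement, not as an error or a demonstrated bias. The ceiling is 25% of assignments certain, about 24 of 98, for someone who knows every earlier arm in the block and stratum. It falls with the cube of the share known, to about 10%, 3% and 0.4% at 75%, 50% and 25%. These figures assume that the strata fill at 60 and 38, that each earlier arm leaks independently, and that the observer knows the position in the block. The article gives no leak rate, so the true figure could be close to zero. The sample size and the planned analysis are not affected.

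**What to change.** For participants still to be randomised, complete the open block in each stratum. Then continue with a new computer-generated table whose block sizes vary at random, for example 4, 6 and 8, and do not disclose the sizes to those who enrol or assess. The benefit is mainly the near-removal of certain assignments; guessing is hardly reduced, so the non-disclosure instruction and independent lamp delivery remain the main protection.

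The cost is one new table and one sentence in the protocol, with no extra participants or visits. The largest possible imbalance at the end of a stratum rises from 6/2 = 3 to 8/2 = 4.

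If recruitment has closed, state the fixed block size as a limitation in the trial report.

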### Statistical analyses

Data will be analysed using SPSS (version to be determined). Participant and baseline characteristics across treatment groups will be compared using analysis of variance (ANOVA) and chi-squared statistics. Analyses of our primary outcome measures will be performed on the basis of intention to treat. The superiority of the bright white-yellowish light condition compared to dim green light condition will be tested using a repeated measures mixed models design. Both treatment (independent of time) and condition*time interaction effects will be evaluated. Repeated measures logistic regression will be applied to test differences in depression remission rates. Preacher and Hayes mediation analysis will be performed to test whether the effects of light therapy are mediated by restoration of the circadian rhythmicity. Post hoc analyses of this study may include subgroup or discriminant analysis to test if participant characteristics can be identified that predict positive effects of light therapy, such as baseline depression severity, baseline depressive symptoms profile, baseline insulin sensitivity, baseline HbA1c, chronotype, or baseline insomnia severity, seasonality of depression and time of year at which the participant was included in the study.

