## Discussion

To the best of our knowledge, we are the first to investigate the effects of light therapy on depressive symptoms and insulin sensitivity in T2D patients with a major depressive episode.

Creating a valid placebo condition is a major challenge in light therapy trials, due to the visibility of light. In previous research various placebo conditions have been used: deactivated air ionisation generators, dim red light placebo conditions, dim white light conditions and inappropriate timing of light therapy [30]. We however decided to use a dim green light condition as placebo for several reasons. Firstly, inappropriate timing of light therapy can be difficult, as phase alterations vary in non-seasonal depression. Secondly, we regard a dim white light condition less credible when compared to a coloured dim light condition, as a coloured glare to the surroundings is absent for a white light condition. Thirdly, a dim red light placebo condition may be less credible nowadays, as much more information on (e.g. on the active spectrum of light) has become available to the public. We considered dim green light a valid placebo condition, reasoning that because the green part of the spectrum around 545 nm is biologically relatively inactive [51], at low intensities there will be no substantial effect, while dim green light will induce positive expectations quite comparable to white light, as was previously shown for dim red light [52].

Participation in the hyperinsulinaemic-euglycaemic clamp experiment is optional, to prevent participants to refrain from participation in our study. This procedure may introduce a selection bias, with potentially psychiatrically and somatically less severely affected participants in the hyperinsulinaemic-euglycaemic clamp subgroup, limiting the generalizability of our findings on insulin sensitivity.

Participants with diabetic retinopathy EURODIAB grade 3–5 will be excluded from participation in this study as a safety precaution. If our study does find positive effects on mood and insulin sensitivity in absence of ocular damage, it may be worthwhile to investigate the effects of light therapy in patients with diabetic retinopathy EURODIAB grade 3–5, as these patients are expected to have a greater risk for depression and poor glycaemic control.

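### The clamp stratum used in randomisation is not named in the IDS model; if it is prognostic and left out, the time-independent treatment test is slightly conservative

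*Protocol article*

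**What the plan says.** Under Randomisation, the protocol article fixes the allocation: "Participants will be randomly assigned to the experimental or placebo condition at a 1:1 ratio", and "Randomisation will be performed in blocks of 6 using a computer-generated table". Allocation "will be stratified for whether a participant will or will not take part in the hyperinsulinaemic-euglycaemic clamp experiment".

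Under Sample size, the insulin-sensitivity question "will be tested in a subsample of 60 participants in total". With 98 participants in all, the strata are therefore planned at 60 and 38.

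The Discussion comments on making the clamp optional: "This procedure may introduce a selection bias, with potentially psychiatrically and somatically less severely affected participants in the hyperinsulinaemic-euglycaemic clamp subgroup". It raises this as a limit on how far the insulin-sensitivity findings generalise, and gives no size.

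Under Statistical analyses, superiority of bright over dim light "will be tested using a repeated measures mixed models design". "Both treatment (independent of time) and condition*time interaction effects will be evaluated". The section lists no covariates for this model: neither the clamp stratum nor baseline IDS is mentioned as a term.

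**The concern.** Blocked randomisation within strata nearly equalises the share of clamp participants in the two arms. If that factor is related to IDS level, the design has removed most of the between-stratum variation from the comparison of arms. A model without the stratum does not know this and leaves that variation in its error term. The reported standard error then exceeds the true one, the confidence interval is too wide and the test rejects too rarely under the null.

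At stake is some efficiency in one of the two effects that the plan says it will test. The Discussion gives a reason to take the possibility seriously, because depression severity is what the IDS measures.

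**Working it through.** **Inputs from the protocol article.** d = 0.50, repeated-measures correlation 0.6, two-sided α 0.05, power 0.80, 42 per arm before attrition, 15% attrition, 98 in total, 60 of them in the clamp subsample (Sample size); blocks of 6, 1:1 (Randomisation); IDS at T0, T1, T2, T3, T4 and T8 (Primary outcome measures).

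**Assumption.** The IDS difference between strata, D, is not given. It is taken as 0.3, 0.5 or 0.8 SD, constant over time.

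**1. The plan's own figure.** n per arm = 2(1.96 + 0.842)² × V / 0.5².
- Mean of six visits: V = (1 + 5 × 0.6)/6 = 0.667, giving n = 41.9, so 42.
- One follow-up visit adjusted for baseline: V = 1 − 0.6² = 0.64, giving n = 40.2, so 41.
- 84/0.85 = 98.8, against the stated 98.

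The stated size reproduces within rounding, and it takes no credit for the stratum.

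**2. Variance explained at one visit.** R² = p(1 − p)D² with p = 60/98, so p(1 − p) = 0.237. This gives 0.021, 0.059 and 0.152 for D = 0.3, 0.5 and 0.8.

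**3. Time-independent effect, taken as the mean of the five post-baseline visits.** The total variance of that mean is (1 + 4 × 0.6)/5 = 0.68. Averaging reduces within-person noise but not the stratum difference, so the stratum's share rises to R²/0.68 = 0.031, 0.087 and 0.223.
- SE reported without the stratum: √(0.68 × 2/42) = 0.180.
- True SE: 0.180 × √(1 − share) = 0.177, 0.172 and 0.159.
- Type I error: 2[1 − Φ(1.96/√(1 − share))] = 0.046, 0.040 and 0.026.

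**4. Simulation.** 8000 runs per scenario, 84 completers split 51/33, blocks of 6 within stratum, total correlation 0.6. Empirical SEs under the null were 0.177, 0.172 and 0.160, and type I error was 0.045, 0.039 and 0.026, in agreement with step 3. Power at d = 0.5, without → with the stratum:

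| Analysis | D = 0.3 | D = 0.5 | D = 0.8 |
|---|---|---|---|
| Post-baseline mean, no baseline term | 0.788 → 0.797 | 0.793 → 0.819 | 0.814 → 0.876 |
| T4 with T0 IDS as covariate | 0.804 → 0.805 | 0.797 → 0.802 | 0.806 → 0.817 |
| Change T0 to T4 | 0.719 → 0.716 | 0.705 → 0.705 | 0.715 → 0.715 |

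A repeat with a new random seed gave 0.807 → 0.877 for the post-baseline mean at D = 0.8, hence 6 to 7 points. If the mean is taken over all six visits, T0 included, the loss is about 1, 3.5 and 10 points (0.642 → 0.654, 0.640 → 0.675, 0.653 → 0.751).

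**5. Why the change test is unaffected.** A constant D is subtracted out of each participant's change. At D = 0.8 the reported and empirical SEs are both 0.195, and type I error stays near 0.05.

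**The case against.** The strongest objection is that silence is not exclusion. The article names a class of model and the effects to be tested, which is not a full list of terms. Covariates are commonly left to an analysis plan, and that plan is not shown. This stands: a reader might infer that the sponsor has decided to omit the stratum, and the document does not say so. What remains is narrower. The article states both the stratification and the model effects, and as published the second does not reflect the first.

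Three other stronger readings also fail.

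- **That the plan expects the strata to differ.** The Discussion is conditional in its wording, gives no size, and does not link clamp participation to change in IDS.
- **That the primary analysis loses power in general.** The plan also tests condition*time, and the Outcome measures section says that changes between visits will be compared. A constant severity difference cancels there. A loss would need the stratum to predict change, which nothing in the document claims.
- **That the trial is underpowered.** A single-visit t-test with 42 per arm has only about 62% power at d = 0.5, but that is not the planned analysis. The stated size reproduces on a repeated-measures basis. Without the stratum, power stays at about 0.79 to 0.81 for both the post-baseline mean and the baseline-adjusted T4 analysis.

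It is also fair to say that stratifying is not wasted without a model term: it supports the equal groups of 30 per arm that the clamp calculation assumes. For remission, analysed by repeated measures logistic regression, the linear-model variance argument does not carry over directly, and adding a covariate changes the odds ratio being estimated.

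**Conclusion.** The point holds as a minor one, on two conditions: the model is run as described, without the stratum, and the stratum is related to IDS level. The test of the time-independent treatment effect without baseline adjustment is then mildly conservative. For the post-baseline mean the loss is about 1, 3 and 6 to 7 points of power at stratum differences of 0.3, 0.5 and 0.8 SD. These differences are assumptions, and every size given here rests on them, on their being constant over time, and on 84 completers.

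The loss is nil for the condition*time contrast and about 0 to 2 points once T0 IDS is in the model. Omitting the stratum forgoes a gain. It introduces no bias and no excess of false positives, and it does not disturb the stated sample size.

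**What to change.** State in the Statistical analyses section, or in the analysis plan, that the randomisation stratum (clamp yes/no, as randomised) is a fixed effect in the IDS mixed model. If the analysis plan already says so, nothing more is needed.

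The term may also be added to the remission model, with a note that the treatment odds ratio is then conditional on stratum. The clamp analysis needs no term, because the stratum is constant there.

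The cost is one degree of freedom. In the simulations no analysis lost meaningful power from adding it; the largest drop, 0.719 to 0.716, is within simulation noise. Naming the term in advance also removes a later choice about covariates.
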